# The prevention of delirium in elderly with obstructive sleep apnea (PODESA) study: protocol for a multi-centre prospective randomized, controlled trial

**DOI:** 10.1186/s12871-017-0465-5

**Published:** 2018-01-03

**Keywords:** Aged, Continuous positive airway pressure, Delirium, Sleep apnea, Obstructive, Perioperative period

## Abstract

**Background:**

Delirium is a common problem that occurs in 5–50% of elderly individuals following surgery. Patients who develop delirium after surgery are at increased risk for serious complications. Recent studies suggest that patients with obstructive sleep apnea (OSA), a sleep disorder characterized by repeated episodes of complete or partial blockage of the upper airway – are at greater risk to develop delirium. OSA is more common in elderly individuals but is often undiagnosed. Identification and treatment of unrecognized OSA may reduce the incidence of postoperative delirium. However, few studies have investigated the effect of perioperative treatment of OSA to prevent postoperative delirium.

**Methods:**

This multi-centre randomized controlled trial will enrol 634 elderly patients undergoing elective hip/knee replacement surgery. The study has been approved by the Research Ethics Boards of the three participating institutions. Patients will be screened with the STOP-Bang questionnaire. Those with a score of 3 or greater will have a portable home sleep study using the ApneaLink™ Air device. Patients identified to have OSA will be randomized to 1) Auto-titrating continuous positive airway pressure (APAP) applied during sleep for 72 h after surgery or until discharge if they are discharged before 72 h **or** 2) Control group – routine care, no APAP. All patients will be evaluated for delirium for 72 h after surgery or until discharge if they are discharged before 72 h. The primary outcome is the occurrence of delirium – assessed twice daily using the Confusion Assessment Method for 72 h or until discharge if the hospital stay is <72 h.

**Discussion:**

Delirium is associated with increased morbidity and mortality, and higher healthcare costs. With the aging population, the incidence of postoperative delirium will likely increase as the number of elderly individuals undergoing surgery rises. The results of our study will be published in a peer-reviewed journal and presented at local and international medical conferences. Our study findings may lead to improved surgical outcomes, enhanced patient safety and reduced healthcare costs.

**Trial registration:**

This study was retrospectively registered at clinicaltrials.gov NCT02954224 on November 3, 2016.

## Background

### Postoperative delirium

Delirium is an acute confusional state, with fluctuating impairment in attention and decreased awareness of one’s environment [1, 2]. Postoperative delirium is a common complication after major surgery; the incidence has been reported to be 13–41% after elective hip or knee replacements, and 26–61% for patients undergoing femoral neck fractures [3, 4]. Postoperative delirium is associated with increased mortality, morbidity, longer hospital stays [5], higher hospital costs [6], cognitive deterioration, and delayed rehabilitation. The pathophysiology of delirium remains poorly understood. The development of postoperative delirium is thought to be a multi-factorial process [7] with a combination of predisposing and precipitating factors. Predisposing factors can be defined as the patient’s baseline vulnerabilities and precipitating factors as injury that occurs throughout the perioperative period [8]. Predisposing factors include sex, age, cognitive status, and coexisting medical conditions, while precipitating factors include surgery, and hypoxia, however, there are few effective preventive measures for delirium [9]. The clinical presentation of delirium varies [10] but postoperative delirium typically occurs on days 2 and 3 after surgery [11, 12].

### Obstructive sleep apnea (OSA)

OSA is a sleep disorder characterized by repeated episodes of complete or partial blockage of the upper airway, resulting in cessation of airflow for at least 10 S*. OSA* is a serious medical condition that is associated with hypertension, stroke, myocardial infarction, diabetes, long term cognitive impairment and lower quality of life [13, 14]. OSA is more prevalent in elderly individuals [15]. In fact, 17% of men and 9% of women aged 50–70 years old are estimated to have OSA [16]. OSA may be under-reported in elderly individuals because some of the symptoms for OSA such as tiredness may be attributed to normal aging.

### Clinical studies of OSA and postoperative delirium

An association between OSA and postoperative delirium was reported in a study on elderly patients undergoing elective knee replacement surgery [11]. In a study of patients undergoing elective cardiac surgery, a preoperative diagnosis of moderate to severe OSA was associated with a 6-fold increased risk of postoperative delirium [17]. In a retrospective study of matched control patients undergoing hip and knee replacement surgery, the incidence of delirium was 2-fold higher and the length of hospital stay was longer, in patients with OSA vs. those without OSA [18]. There are also several case reports of patients with acute delirium and OSA that resolved with treatment of OSA by continuous positive airway pressure (CPAP) [19–21]. A recent trial of elderly surgical patients at risk for OSA who were randomly assigned to either CPAP or routine care reported that OSA and apnea are associated with postoperative delirium, however, they did not find a reduction in postoperative delirium with CPAP [22]. It should be noted that in this trial, the diagnosis of OSA was not confirmed with a sleep study and the compliance with CPAP was low – which may have led to the lack of a difference between the CPAP and no CPAP group. Therefore, it is unclear from previous studies whether diagnosis and treatment of OSA with CPAP will decrease the incidence of post-operative delirium in elderly patients. Precipitating factors for postoperative delirium in patients with untreated OSA may include hypoxia and disrupted sleep that is worsened by inflammation from surgery, pain and opioid analgesics.

### Treatment of OSA and auto-titrating CPAP

Among the different treatments for OSA, auto-titrating continuous positive airway pressure (APAP) is widely used. It is highly effective in eliminating OSA, and alleviating its symptoms including daytime sleepiness, cognitive function and overall quality of life [23, 24]. APAP adjusts the pressure delivered to the patient based on a breath-by-breath measurement of airflow to maintain the minimal pressure required to keep the upper airway unobstructed. Studies have reported that starting treatment with APAP can be just as effective as CPAP titrated during polysomnography (PSG) [25–27].

### Objectives

The objectives of this trial are to identify OSA preoperatively with a portable home sleep study and to determine whether APAP treatment of OSA will decrease the incidence of post-operative delirium in elderly individuals undergoing elective hip or knee replacement surgery.

## Methods

### Trial design

The **P**revention **O**f **D**elirium in **E**lderly with Obstructive **S**leep **A**pnea (PODESA) study is a multi-centre, prospective, randomized controlled superiority trial with two parallel groups. Randomization at each site will be performed with a 1:1 allocation into intervention (APAP) or control (routine care) group. The overall study design is shown in Fig. 1.

**Fig. 1 Fig1:**
[figure not shown]
Flow chart of study. ESS: Epworth Sleepiness Scale; OSA: obstructive sleep apnea; APAP: auto-titrating continuous positive airway pressure; AHI: apnea-hypopnea index

### Study setting

This ongoing study is being conducted at three academic hospitals: Toronto Western Hospital, University Health Network; Mount Sinai Hospital; and Sunnybrook Hospital located in Toronto, Ontario Canada over 3 years. The target completion date is December 2018.

### Eligibility criteria

Inclusion criteria for participation include patients who are: 1) 60 years and older; 2) scheduled for elective hip or knee replacement surgery at least 4 working days after the preoperative clinic visit; 3) possess the cognitive and physical capability necessary to comprehend and complete the study questionnaires; 4) proficient in English with a reading level at Grade 6 (patient or accompanying person); 5) accessible for follow-up via telephone, or via the Internet; and 6) able to provide informed consent.

The exclusion criteria include patients with schizophrenia or active psychosis within the last 3 months, current use of antipsychotic medication, anxiety disorders, poorly controlled depression, multiple psychiatric disorders, a history of drug or alcohol dependence or abuse within the last 3 months, dementia, and/or clinically significant neurological disorders (stroke, epilepsy, brain tumours, Parkinson’s Disease etc.). Other exclusion criteria include patients undergoing surgery that is two-staged involving more than one surgical procedure to be performed within the same hospitalization period, central sleep apnea (more than 50% central events, or with significant Cheyne-Stokes respiration pattern), significant cardiac disease (New York Heart Association functional class III and IV, severe valvular heart disease, dilated cardiomyopathy, implanted cardiac pacemaker, unstable angina), myocardial infarction or cardiac surgery or percutaneous coronary intervention within 3 months, severe tracheal or lung disease, or a contraindication to the APAP facemask. Patients with a prior diagnosis of sleep-related breathing disorder who are compliant with CPAP/APAP treatment will be excluded. However, patients who have had prior sleep studies may be included if they have been lost to follow-up by a sleep physician, are not on treatment or are non-compliant to treatment (mean CPAP or APAP nightly use <4 h, or median nightly CPAP or APAP use <50% of total sleep time) [28].

### Patient screening and baseline assessment

Trained research assistants will screen patients who are scheduled for elective hip or knee replacement surgery in each site for eligibility to participate in the study. There will be no financial or non-financial incentives provided to participants for enrolment. Those interested in participating in the study will be given written information about the study, including the objectives and procedures. Research assistants will ask patients to provide written informed consent prior to collection of the baseline assessment.

In the preoperative clinics, all patients who consent will complete the STOP-Bang questionnaire [29, 30], Epworth Sleepiness Scale [31], Charlson comorbidity index [32], and Mini-Cog Test [33, 34]. The STOP- Bang Questionnaire is a validated questionnaire to screen patients for OSA [29]. If a patient has a STOP-Bang score of 3 or higher, they will have a portable home sleep study with ApneaLink™ Air (ResMed, San Diego, California, USA) for one night. ApneaLink™Air is a Type III sleep apnea monitoring device that records the following data: nasal airflow, snoring, blood oxygen saturation, pulse and respiratory effort during sleep.

The sleep data will be manually scored and checked by a qualified sleep technologist, and interpreted by the study sleep physician for recordings of at least 3 h duration. In the case of inadequate sleep or any technical failure, the patient will repeat the Apnea LinkAir™ study once. The conduct, data retrieval and interpretation of the sleep study will be guided by the current Canadian Sleep Society [35] and American Academy of Sleep Medicine [36] guidelines for portable monitors. The scoring criteria for breathing events will be guided by the American Academy of Sleep Medicine definition [37]. An apnea is defined as a decrease in airflow by ≥90% of baseline for ≥10 s. A hypopnoea is defined as a decrease in airflow by >30% baseline for ≥10 s in association with either ≥3% oxygen desaturation from pre-event baseline and/or the event is associated with an arousal [37].

Oximetry monitoring with a high-resolution pulse oximeter wristwatch (PULSOX-300i, Konica Minolta Sensing, Inc., Osaka, Japan) will be carried out for one night before surgery and for three nights postoperatively or until discharge if the hospital stay is <72 h.

### Definition of OSA

Patients will be defined as having OSA if the apnea-hypopnea index (AHI) is ≥ 10/h on the ApneaLink™ Air study. Patients with AHI < 10/h will be excluded from further study.

### Interventions

Patients identified to have OSA (AHI ≥ 10/h) will be randomised to receive APAP or control (routine care).

APAP: APAP will be applied during day/night sleep for 72 h after surgery or until discharge if the hospital stay is <72 h. The ResMed AirSense 10 Autoset device (ResMed San Diego, California, USA) is the APAP device that will be used for the study. The Airview™ server (ResMed, San Diego, California, USA) will be used to monitor the APAP compliance, AHI, mask leakage and breathing events.

Control (routine care): will receive standard care by the health care team, and no APAP. The standard of care may include oxygen therapy, or any other procedures or consultations as deemed necessary by the health care team as needed.

### Assignment of interventions

A computer generated randomization list for each participating site will be created by a research analyst who is not involved in the study. The patient assignments will be placed in serially numbered, opaque-sealed envelopes corresponding with the randomization schedule for each site. The research assistant will open the envelope after the sleep study confirms the diagnosis of OSA for the patient.

### Blinding

It is not possible to provide an ‘active placebo’ for the control group since it is not possible to program the APAP to zero cm H_2_O. Statisticians and study investigators performing data analysis will remain blinded. If any adverse event or complication occurs necessitating discontinuing the study intervention, this will result in voluntary un-blinding of outcome assessors.

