### Primary outcomes

The primary outcome is postoperative delirium. The diagnosis of postoperative delirium will be based on using the Confusion Assessment Method (CAM) [2]. CAM has been validated against the Diagnostic and Statistical Manual Disorders Fourth Edition. All patients will be evaluated for delirium with the CAM 2 times daily, for 72 h or until discharge if the hospital stay is <72 h, by trained research assistants. These assessments will be done on post-operative nights 1, 2 and 3 or until discharge (if the hospital stay is <72 h), with at least 6 h between assessments. The first assessment for delirium will be performed when patients can be sufficiently aroused (Richmond Agitation and Sedation Score > −4) [38] in order to be assessed for delirium on the day of surgery [39, 40]. If the patient’s delirium persists beyond 72 h after surgery, he/she will be assessed with the CAM twice daily until the delirium resolves.

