### Adherence

Patients in the intervention group will be reminded in each study visit the importance of adherence to APAP therapy.

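### The blind that the protocol implies for CAM raters is not protected, and its own rule un-blinds them when an adverse event or complication stops APAP

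*Protocol article*

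**What the plan says.** All references are to the Methods of the protocol article.

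- **Blinding.** No sham APAP is possible. The roles named as blinded are those handling the data: "Statisticians and study investigators performing data analysis will remain blinded". The next sentence gives a trigger, "If any adverse event or complication occurs necessitating discontinuing the study intervention", and its consequence: "this will result in voluntary un-blinding of outcome assessors".
- **Assignment of interventions.** "The research assistant will open the envelope after the sleep study confirms the diagnosis of OSA for the patient".
- **Primary outcomes.** CAM is done twice a day, "for 72 h or until discharge if the hospital stay is <72 h, by trained research assistants". The timing is then given as follows: "These assessments will be done on post-operative nights 1, 2 and 3 or until discharge", with at least 6 h between assessments. The first assessment waits until the patient can be aroused.
- **Interventions.** "APAP will be applied during day/night sleep for 72 h after surgery or until discharge". Controls get no APAP.
- **Adherence.** "Patients in the intervention group will be reminded in each study visit the importance of adherence to APAP therapy". The person giving the reminder is not named.

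**The concern.** Un-blinding can only happen to someone who is blinded, so the Blinding section treats CAM raters as blinded without saying so. The same section then removes that blind through an event that can occur in one arm only. Other sections leave the blind unguarded in three ways: a shared role, a shared time window with a visible device, and contact specific to the APAP arm at study visits.

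CAM depends on the rater's judgement. Patients and ward staff know the arm because there is no sham. Blinding the analysts does not repair a rating already made with knowledge of the arm. If raters who know the arm score APAP patients more leniently, the trial can show a reduction in delirium that APAP did not cause.

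**Working it through.** **1. The un-blinding rule.** The trigger is stopping the study intervention because of an adverse event or complication. The control group receives routine care and has no study device to stop. The rule therefore operates only in the APAP arm, and a rater told of the stop knows the allocation. Primary outcomes continues CAM past 72 h until delirium resolves, so ratings can still be due after the un-blinding. The Blinding section gives no reason why the CAM rater needs the allocation at that point.

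**2. Roles.** Assignment of interventions gives the envelope to the research assistant. Primary outcomes gives CAM to trained research assistants. Neither these sections nor Standardization of training says that they are different people for a given patient.

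**3. Timing.** APAP use and CAM share the same 72 h, and CAM is placed on nights. The mask is for sleep and CAM needs a patient who can be aroused, so sight of the device is likely rather than certain.

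**4. The plan's own sample size.** Inputs from Sample size: 24% versus 9.9%, power 0.8, alpha 0.05 (two-sided assumed). The mean rate is 0.1695.

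n = [1.960·√(2·0.1695·0.8305) + 0.842·√(0.24·0.76 + 0.099·0.901)]² / 0.141² ≈ 110 per group.

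The stated 110 reproduces, and this point does not change it.

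**5. Illustration of the stake.** Assumptions, none from the documents: true delirium 20% in both arms; control patients rated with sensitivity 95% and false positives 5%; every APAP patient rated by someone who knows the arm. The 110 per arm and the 0.05 level are the plan's.

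Observed rate = 0.20 × sensitivity + 0.80 × false-positive rate.

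Control: 0.20 × 0.95 + 0.80 × 0.05 = 23.0%.

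P(false APAP benefit) ≈ Φ[(d − 1.960·s0)/s1]. Here d is the observed difference, s0 = √(2·p̄(1 − p̄)/110) and s1 = √([pC(1 − pC) + pA(1 − pA)]/110).

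| APAP-arm sensitivity / false positives | Observed APAP rate | Spurious difference | Chance of a false benefit (exact enumeration) |
|---|---|---|---|
| 95% / 5% (no bias) | 23.0% | 0 | 2.5% |
| 85% / 5% | 21.0% | 2.0 points | 5.3% |
| 90% / 3% | 20.4% | 2.6 points | 6.6% |
| 85% / 2% | 18.6% | 4.4 points | 12.2% |
| 75% / 2% | 16.6% | 6.4 points | 21.9% |

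Worked for the last row: d = 0.064, s0 = 0.0537, s1 = 0.0536. Then (0.064 − 0.1053)/0.0536 = −0.77, and Φ = 0.22, which agrees with the exact 21.9%. The 6.4 points are 6.4/14.1 = 45% of the planned difference (24% − 9.9% = 14.1 points).

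The spurious difference scales with the share of APAP patients rated by someone who knows the arm. At one half, the last row falls to 3.2 points.

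**The case against.** The strongest reply is that this is a condensed article. Who does which task on the ward is commonly left to the full protocol, and a shared job title is not a shared person. Standardization of training refers to those research assistants who assess delirium, which allows for others who do not. That stands against any claim that the same individual opens the envelope and rates the patient. It does not answer the un-blinding rule, which is written text and not an omission.

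A reader might infer more than the documents support on five further points:

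- **That assessor blinding is promised.** It is implied only; the named blinded roles are the statisticians and the investigators analysing data.
- **That CAM is done with the mask on.** APAP is for sleep and CAM needs an aroused patient, so this is inference. The nights may be only labels for the 72 h window, so they do not firmly contradict two assessments a day at least 6 h apart. The wording is unclear and needs reconciling.
- **That CAM raters give the adherence reminders.** The Adherence section does not say who does.
- **That every stop of APAP un-blinds the rater.** The rule covers stops forced by an adverse event or complication, and calls the un-blinding voluntary. Risk is expected to be low, so few patients may be affected.
- **That the blinded rater is the only safeguard.** The plan also has a validated instrument, psychiatrist-led training with a supervised first interview, sealed envelopes and blinded analysts. None of these stops a rater who knows the arm from being influenced by it.

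The size is also open to challenge. The 12% and 22% figures need sensitivity and false positives both to move in APAP's favour in every APAP patient. With sensitivity alone falling to 85%, the figure is about 5%.

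**Conclusion.** The point holds in this form: the protocol implies blinded CAM raters, states a rule that reveals the arm to them after certain events in the APAP arm only, and gives no protection elsewhere for the blind it implies. The un-blinding rule is the firmest part because it rests on the text alone. The shared role and the overlap in time show that the blind is unprotected; they do not show that it is broken.

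No size can be derived from the documents. Under the stated assumptions, the chance of a false APAP benefit runs from 2.5% with no bias, through about 5%, to about 22%. These figures describe a loss of the blind across the whole APAP arm. They do not measure the un-blinding rule alone, which touches only patients whose APAP is stopped for an adverse event or complication. The sample size is unaffected.

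**What to change.** 1. Delete the sentence that un-blinds outcome assessors, so that CAM raters stay blinded when APAP is stopped. This costs nothing and leaves the management of the event untouched.
2. State that CAM raters are blinded. Within the existing research-assistant team, whoever opens the envelope, sets up APAP or gives adherence reminders does not perform CAM on that patient. The cost is some rota inconvenience, mostly where the team is small.
3. Reconcile the nights wording with the twice-daily wording in Primary outcomes. State that patients are assessed awake, with the device out of view where feasible. The study is ongoing, so record the date of any real change in timing, because it would alter how the primary outcome is ascertained part-way through.
4. Have the rater record a guess of allocation, so that the success of blinding can be reported. This adds one item to the form.
5. If blinding cannot be kept, say that the primary outcome is assessed unblinded and limit the conclusion accordingly.

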### Perioperative management of patients in both groups

There will be no change to the usual surgical, anaesthetic or postoperative pain management of patients in both groups at the participating centers.

There will be a phone follow up 30 days after discharge from hospital to document any complications.

